### Surgical operation

The same senior spine surgeon will carry out all surgeries. Patients will receive general anesthesia before surgery using the common right-sided anterior cervical approach with their necks in a neutral position. An anterior technique will be used to perform discectomy and decompression at the index level by removing osteophytes, the posterior longitudinal ligament, and disc tissues. A decompression procedure will be initially performed if the degenerative segment is more severe. For CDA, after preparing end plates and disc space with burrs, tests, implant tests, and rail cutter guide. Next, the channels in the end plates and a Prestige LP disc of the proper size will be installed (Medtronic Sofamor Danek, Memphis, TN, USA). For the ACDF approach, the intervertebral space will be filled using Zero-P (Synthes, Oberdorf, Switzerland) implants packed with tricalcium phosphate or locally removed bone. All prostheses will be implanted with the aid of fluoroscopy.

### Outcomes

#### Primary outcome

We chose the Neck Disability Index (NDI) functional score as the primary study endpoint. The NDI was proven to have better reliability, validity, and responsiveness for self-rated disability for postoperative patients [34]. The NDI will be evaluated postoperatively and at the 1^st^ week, 3^rd^ week, 6^th^ week, 3^rd^ month, 6^th^ month, and 12^th^ month after surgery. The NDI consists of ten items, including pain intensity, personal care, lifting, sleep, driving, recreation, headaches, concentration, reading, and work. Each item is scored out of 5 for a maximum total score of 50. Neck functions will be assessed by this score for all patients [35].

#### Secondary outcomes

The secondary outcomes will include clinical, radiologic, and complication assessments. The assessment will be conducted prior to the operation and subsequently after the operation, continuing up to a period of 12 months post-operation or until the conclusion of the study (Table 1 and Fig. 2). The clinical and radiologic examinations will be performed by investigators who have no therapeutic relationship with the individual patient. All radiographs will be examined independently by one radiologist.

**Table 1 Tab1:** Data collection

Variables	Baseline	Follow-ups					
	Preoperation	1^st^ week	3^rd^ week	6^th^ week	3^rd^ month	6^th^ month	12^th^ month
Screening for inclusion and exclusion criteria	√						
Informed consent	√						
Randomization	√						
Baseline demographics	√						
Information collected through telephone follow-up/subjective scales							
NDI	√	√	√	√	√	√	√
JOA	√	√	√	√	√	√	√
VAS	√	√	√	√	√	√	√
PSQI	√	√	√	√	√	√	√
BDS	√	√	√	√	√	√	√
FES	√	√	√	√	√	√	√
Information collected through questionnaire follow-up/subjective scales							
SF-36	√	√	√	√	√	√	√
Cervical collar satisfaction score		√	√	√	√	√	√
Information collected through physical examination/objective scales							
Neck soft tissue assessment	√	√	√	√	√	√	√
Braden Scale		√	√	√	√	√	√
Information collected through radiologic examinations							
Cervical lordosis	√	√		√	√	√	√
ROM of C2-C7	√	√		√	√	√	√
Disc angle of the operative levels	√	√		√	√	√	√
ROM of the operative levels	√	√		√	√	√	√
ROM of the adjacent levels	√	√		√	√	√	√
Disc height of the operative levels	√	√		√	√	√	√
Fusion rate		√		√	√	√	√
Complications							
Anterior bone loss		√	√	√	√	√	√
Prosthesis migration		√	√	√	√	√	√
Heterotopic ossification		√	√	√	√	√	√

*JOA* Japanese Orthopedic Association, *NDI* Neck Disability Index, *VAS* visual analog scale, *PSQI* Pittsburgh Sleep Quality Index, *BDS* Bazaz dysphagia scoring system, *FES* Falls Efficacy Scale, *SF-36* MOS 36-item short-form health survey, *ROM* range of motion

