#### Radiologic examinations

9.Cervical lordosis: It was defined as the angle between the inferior end plate of C2 and the inferior end plate of C7. Patients need to take radiographs of the cervical spine function position.10.Disc height of the operative levels: Intervertebral space height equals one-third of the sum of anterior intervertebral space height, middle intervertebral space height and posterior intervertebral space height (Fig. 3)11.Cobb angle and ROM (Table 2 and Fig. 3) [42, 43].12.Bony fusion: Bony fusion is defined as continuous trabecular bone formation on cervical vertebrae reconstruction CT, cervical intervertebral range of motion of full extension and flexion of less than 2° and radiolucency covering the implant’s outer surfaces of less than 50%. All criteria must be met for a joint to be considered effectively fused [44, 45].

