#### Complications

13.Anterior bone loss: It was as a combined standard of the percentage of the endplate length and implant subsidence [44] (Table 1).14.Prosthesis migration: It was defined as the sum of the change in the height of the cranial and caudal vertebral body between the immediate postoperative and follow-up situations on lateral radiographs. A level was classified as subsided if the measured subsidence was > 2 mm. Anteroposterior migration is defined as the sum of the cranial and caudal translation of the prosthesis with respect to the corresponding endplates between the immediate postoperative and follow-up situations on lateral radiographs. A prosthesis was classified as migrated if the anteroposterior migration was > 3 mm [45].15.Heterotopic ossification (HO): HO at the index level will be evaluated using the scoring system established by Mehren et al. [46] (Table 1).

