### Statistical analysis

We used SPSS version 20.0 (IBM Corp, Armonk, NY, USA) for standard statistical analyses. Quantitative variables are presented as the mean ± standard deviation when normality is met. We used one-way analysis of variance (ANOVA) to compare quantitative data. If *p* < 0.5 for ANOVA, LSD or Dunnett’s test was used to compare means. Chi-square analysis or Fisher’s exact test was used to compare qualitative data, and paired sample *t*-tests were used for the same group. Comparisons of unidirectional orderly data were analyzed using the Wilcoxon signed-rank test. Two-sided *P* values were reported when comparing differences between the 2 groups. *P* value < 0.05 was considered of statistical significance.

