## Discussion

External cervical brace fixation is often performed after anterior cervical surgery to provide biomechanical support to maintain spinal physiological curvature and stability, avoiding complications such as laryngeal edema and hematoma [47, 48]. There is still some debate regarding whether cervical collars should be used following surgery [24]. Previous studies have shown that the use of a cervical collar can reduce the risk of graft nonunion, graft displacement and sinking. At the same time, it can also restrict neck movement, providing spinal stability, reducing pain, and even increasing the sense of security in patients [20, 49]. Despite these benefits, some researchers have contested their validity. In their study, they found that patients with cervical pain that did not wear a cervical collar did not have a lower VAS score than those who wore a collar for 2 weeks. Moreover, the JOA score, SF-36, ROM, anterior convex angle, and complications were comparable between these two groups [50, 51]. In addition, wearing cervical collars can also bring many complications to patients, such as skin injuries skin ulcers, impaired daily activities and sleep, and decreased lung capacity and function [52–54].

Because there are no scientific clinical trials verifying the efficacy of cervical collars after hybrid surgery [20, 24, 26, 55–57], to explore the effect of wearing neck braces after undergoing hybrid surgery and discuss the best wearing time for recovery, we designed this randomized controlled trial, hoping to gain scientific and accurate results about the physical, functional, and quality of life-related outcomes of patients.

The process of osseointegration involves the direct structural and functional connection between living bone and the implant. This is normally initiated 6 weeks postoperatively, while the bone-graft bone bridge forms in around 3-month time. Therefore, most complications, including graft subsidence and loss of cervical lordosis appear during the first 6 weeks following surgery [58–60]. Thus, 3 months post-surgery is a critical time for recovery. In that case, the collar immobilization times were all set within 3 months post-surgery. Then, we adjusted the wearing time of the cervical collar to 3 weeks, 6 weeks, and 12 weeks.

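### Disc height and cervical lordosis have no postoperative reference in the between-arm analysis, so spread from the surgery itself lowers precision on loss after surgery

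*Protocol article*

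**What the plan says.** Under Radiologic examinations, disc height is the average of three readings on one film: "Intervertebral space height equals one-third of the sum of anterior intervertebral space height, middle intervertebral space height and posterior intervertebral space height". Of lordosis the same section says: "It was defined as the angle between the inferior end plate of C2 and the inferior end plate of C7". Neither definition contains a change or a postoperative reference.

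Table 1 schedules both measures, the first under the row "Disc height of the operative levels", before surgery, at weeks 1 and 6, and at months 3, 6 and 12. Neither Table 1 nor the Follow-up time section lists an immediate postoperative film.

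Statistical analysis gives one rule for comparing arms on such data: "We used one-way analysis of variance (ANOVA) to compare quantitative data". It names no covariate. Within an arm, "paired sample *t*-tests were used for the same group"; the visits to be paired are not stated.

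Three other places bear on the point:

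- Surgical operation: at arthroplasty levels, "a Prestige LP disc of the proper size will be installed". The operated disc is removed and the implant is fitted to the patient.
- Discussion: "most complications, including graft subsidence and loss of cervical lordosis appear during the first 6 weeks following surgery". This is part of the reason given for setting the collar periods within three months.
- Complications: subsidence and migration are measured as change "between the immediate postoperative and follow-up situations on lateral radiographs", then classified at more than 2 mm and more than 3 mm.

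**The concern.** A collar can act only on what happens after the operation. At follow-up, operated-level height and C2-C7 alignment each combine what the surgery achieved with what has been lost since. The first part varies between patients for reasons unrelated to the collar, such as anatomy, implant size and degree of correction. An unadjusted comparison leaves all of that variation in the error term.

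The article recognises the right reference elsewhere, since it measures subsidence from the immediate postoperative film. It does not carry that reference over to disc height or lordosis. At stake is a real collar effect on loss of height or alignment being hidden by avoidable noise in small arms.

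There is a second risk. If a paired test sets the preoperative value against follow-up, it mixes surgical correction with later loss in every arm. Such a result cannot show whether a collar preserved anything.

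**Working it through.** **Plan's own figure.** The article gives no SD, correlation, expected difference or power for disc height or lordosis, so there is nothing to reproduce. Its sample size was set for the NDI and is used here only for the arm size: 20 per arm, or 20 × 0.8 = 16 after the stated 20% dropout.

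**Bias or noise?** Write follow-up value = P − L, where P is the value just after surgery and L is the later loss. Table 1 places randomisation before surgery. If the surgery does not depend on the arm, P has the same expected value in every arm. The expected arm difference in follow-up value then equals, with opposite sign, the expected arm difference in L. P contributes no systematic error, only variance and chance imbalance. In SD units of P, the standard error of the chance difference between two arm means is:

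- 20 per arm: √(2/20) = 0.32 SD
- 16 per arm: √(2/16) = 0.35 SD

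**Gain from adjustment.** Let r be the correlation between the immediate postoperative and follow-up values (assumed; not in the article). Relative to the unadjusted comparison, the variance is:

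- ANCOVA on the postoperative value: 1 − r²
- simple change from the postoperative value, equal SDs: 2(1 − r)

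For two arms of 16, with the error term from all four arms (64 − 4 = 60 df), the 95% CI half-width is t(0.975, 60) × √(2/16) × √(1 − r²) = 0.707 × √(1 − r²) in SD units. The single degree of freedom spent on the covariate is ignored. The difference detectable with 90% power (two-sided 5%, normal approximation) is (1.960 + 1.282) × √(2/16) × √(1 − r²) = 1.15 × √(1 − r²).

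| r | Variance ratio 1 − r² | CI half-width (SD) | Detectable difference (SD) | Equivalent sample multiplier 1/(1 − r²) |
|---|---|---|---|---|
| 0 (unadjusted) | 1.00 | 0.707 | 1.15 | 1.00 |
| 0.3 | 0.91 | 0.675 | 1.09 | 1.10 |
| 0.6 | 0.64 | 0.566 | 0.92 | 1.56 |
| 0.8 | 0.36 | 0.424 | 0.69 | 2.78 |
| 0.9 | 0.19 | 0.308 | 0.50 | 5.26 |

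**Why ANCOVA rather than a change score.** The change-score ratio 2(1 − r) is 1.40 at r = 0.3, 1.00 at r = 0.5 and 0.20 at r = 0.9. A change score is worse than the raw value below r = 0.5. Apart from the spent degree of freedom, ANCOVA is at least as precise at any r. Change from the preoperative value would not help, because it still contains the surgical correction.

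**The case against.** The strongest objection is that the article never says these measures are compared as raw values at each visit. The radiology section describes how a film is read, and an ANOVA of quantitative data could be run on changes. A full analysis plan might settle this. It stands as a caution: the raw-value reading is inferred from the definitions together with the ANOVA sentence. It is still the natural reading, because the article fixes both variable and test, and neither mentions a reference or a covariate.

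A reader might go further and infer that the arm comparison mainly measures implant size and surgical correction. The documents do not support that. Patients are randomised and one surgeon performs all operations, so these factors add variance and not bias unless the surgery differs by arm. The Blinding section does not name the surgeon among the blinded roles, so balance should be checked, but nothing in the text indicates dependence.

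A reader might also infer that the paired tests run from the preoperative visit. The article does not name the visits, and Table 1 would equally allow week 1 against month 12.

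Three further points stand in part. The subsidence item already captures some height loss, but as a yes/no outcome and not for lordosis. The argument from implant size is weaker for lordosis, since a C2-C7 angle is not confined to the operated disc; there the argument rests on surgical correction. The size of the gain is assumption only, and at r = 0.3 it is slight.

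**Conclusion.** The point holds as one of precision and of fit to the trial's question. The stated definitions and the unadjusted ANOVA leave variation created by surgery in the error term, although the stated interest is loss after surgery and the article already uses the right reference film for subsidence. It does not hold as a claim of bias.

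The benefit ranges from about 10% more effective sample at r = 0.3 to about five times at r = 0.9. This assumes an r that the documents do not give, surgery independent of arm, and 16 completers per arm. The trial is described as exploratory and the NDI is untouched, so this is a worthwhile improvement to secondary analyses and not a threat to the main result.

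**What to change.** - For disc height of the operative levels and for cervical lordosis, compare arms on the follow-up values by ANCOVA, with the immediate postoperative value as covariate.
- Add the immediate postoperative film to Table 1. The subsidence and migration definitions already require it.
- Use the week-1 value only as a sensitivity reference. Collar wear may already have begun by then, and the Discussion places most such loss in the first 6 weeks, so adjusting for week 1 can remove part of the effect.
- State that no preoperative-to-follow-up paired t-test will be read as evidence about the collar for these two measures.

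The cost is analysis wording, one Table 1 entry, and reading both measures on a film the plan already relies on. The downside is small: the covariate is measured after randomisation, so the report should show that it is balanced across arms.

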**Fig. 2 Fig2:**
[figure not shown]
SPIRIT figure of this trial

### Clinical examinations

#### Subjective scales

JOA: The JOA score is used to evaluate the neurological status of patients with myelopathy. The JOA of the cervix has 4 main parts: upper and lower limb motor function and sensory and bladder function [35, 36].SF-36: In addition to the JOA, SF-36 is intended to serve as a general health status indicator. The validity and reliability of the SF-36 have also been established in patients with cervical myelopathy [37].VAS: VAS scores will be used to assess neck and upper limb pain in all patients [38].Pittsburgh Sleep Quality Index, PSQI: The PSQI is considered an accepted reference or gold standard for self-perceived sleep quality [39].The Bazaz dysphagia scoring system.Falls Efficacy Scale: It is designed to measure self-perceived fear of falling during l4 common activities [40].Cervical collar satisfaction score: It is designed to evaluate whether participants are content with cervical collars use.

#### Objective scales

8.Neck soft tissue assessment and the Braden Scale will be used to evaluate Neck soft tissue injury extent within 10 cm around the collar position of patients in the collar groups [41] (Table 1 and Fig. 2).

#### Radiologic examinations

9.Cervical lordosis: It was defined as the angle between the inferior end plate of C2 and the inferior end plate of C7. Patients need to take radiographs of the cervical spine function position.10.Disc height of the operative levels: Intervertebral space height equals one-third of the sum of anterior intervertebral space height, middle intervertebral space height and posterior intervertebral space height (Fig. 3)11.Cobb angle and ROM (Table 2 and Fig. 3) [42, 43].12.Bony fusion: Bony fusion is defined as continuous trabecular bone formation on cervical vertebrae reconstruction CT, cervical intervertebral range of motion of full extension and flexion of less than 2° and radiolucency covering the implant’s outer surfaces of less than 50%. All criteria must be met for a joint to be considered effectively fused [44, 45].

**Fig. 3 Fig3:**
[figure not shown]
Measurement of cervical lordosis, disc angle of the operative levels, ROM, and disc height of the operative levels. 1**a** Angle of C2-C7 Cobb includes drawing a line either parallel to the inferior endplate of C2 or another line parallel to the inferior endplate of C7. Perpendicular lines are then drawn from each of the 2 lines noted above, and the angle subtended between the crossing of the perpendicular lines is the cervical curvature angle. 1**b** A line was drawn either parallel to the superior endplate of the operative upper vertebra (OUV) or another line was drawn parallel to the inferior endplate of the operative lower vertebra body (OLV). Perpendicular lines are then drawn from each of the 2 lines noted above, and the angle subtended between the crossing of the perpendicular lines is the cervical curvature angle. The ROM is defined as the difference in Cobb angle between flexion and extension in lateral radiographs. 1**c** The intervertebral space height equals one-third of the sum of the anterior intervertebral space height (a), middle intervertebral space height (b), and posterior intervertebral space height (c). Intervertebral space height = (a + b + c)/3

**Table 2 Tab2:** The measurement method of Cobb angle and ROM

Items	Definitions
Cobb angle	The angle between the lower endplate of the upper vertebral body and the upper endplate of the lower vertebral body
ROM	The difference in Cobb angle between full flexion and extension in lateral radiographs
ROM of the operative levels	The difference in Cobb angle of the operative levels between full flexion and extension in lateral radiographs
ROM of the adjacent levels	ROM of the adjacent (upper and lower) levels of operative levels

*ROM* range of motion

#### Complications

13.Anterior bone loss: It was as a combined standard of the percentage of the endplate length and implant subsidence [44] (Table 1).14.Prosthesis migration: It was defined as the sum of the change in the height of the cranial and caudal vertebral body between the immediate postoperative and follow-up situations on lateral radiographs. A level was classified as subsided if the measured subsidence was > 2 mm. Anteroposterior migration is defined as the sum of the cranial and caudal translation of the prosthesis with respect to the corresponding endplates between the immediate postoperative and follow-up situations on lateral radiographs. A prosthesis was classified as migrated if the anteroposterior migration was > 3 mm [45].15.Heterotopic ossification (HO): HO at the index level will be evaluated using the scoring system established by Mehren et al. [46] (Table 1).

### Data collection

To ensure a satisfactory follow-up rate, we chose telephone follow-up to evaluate the NDI, JOA, VAS, Pittsburgh sleep quality index, the Bazaz dysphagia scoring system, Falls Efficacy Scale, and cervical collar satisfaction score. Since responding to many items is time-consuming for patients, the SF-36 health survey will be collected through questionnaires. When collecting data, the repeated parts will be asked only once to lower the confusion and improve the follow-up rate. Complications and cervical imaging parameters need to be evaluated through radiographs and CT. For a higher follow-up rate, healthcare professionals are to be reminded regularly (Table 1 and Fig. 2).

### Follow-up time

Clinical data were collected preoperatively and at routine postoperative intervals of 1, 3, 6 weeks, 3, 6, and 12 months, as well as at the last follow-up visit. Radiographs and CT scans were routinely taken preoperatively and at postoperative intervals of 1, 3, and 6 weeks and 3, 6, and 12 months as well as at the last follow-up period.

### Oversight and supervision

The study is under the supervision of the research team, comprising orthopedic surgeons, radiologists, data analysts, and other pertinent staff. In terms of research quality control and quality assurance, the primary research team members will convene on a monthly basis to ensure the smooth operation of the trial.

### Data monitoring

An independent committee will monitor data annually. Any event that has a reasonable, causal relationship to the study intervention, including pressure ulcers, mild swallowing difficulty, coughing, muscle stiffness, nerve palsy, pseudarthrosis, and vertebral body collapse, will be deemed an adverse event and promptly reported to investigators for evaluation. In accordance with the stipulations pertaining to anticipated, severe, and causal occurrences, adverse events are thoroughly recorded, fully processed, tracked, and reported to the Ethics Committee promptly until properly resolved or stable. The principal investigator will conduct a cumulative review of all adverse events once a quarter and convenes an investigator meeting to assess the risks and benefits of the study when necessary. No formal audit is scheduled for this trial.

